In the present study, we modified the traditional SMS formula used for CVD (ginseng, Ophiopogon japonicus, and Schisandra chinensis) based on clinical experience, classic texts, and experiment findings. We removed ginseng and added Platycodon grandiflorus and Pueraria lobata as well as Dioscorea opposita and Coix lacrymajobi to stimulate digestive functions. The formula consisting of **Pueraria lobata (5.33g), Platycodon grandiflorus (5.33g), Ophiopogon japonicus (5.33g), Dioscorea opposita (2.67g), Coix lacrymajobi (2.67g), and Schisandra chinensis (2.67g) (total 24g; unit g/day)** is referred to as saengmaeksangagambang (modified SMS), and this prescription is empirically used at Kyung Hee Bi, Che, Dam Korean Medicine Clinic to treat CVD or autonomic nervous system symptoms. The ingredients are prepared as a decoction with alcohol as a solvent, in accordance with the concept of principal and ministerial inversion in Korean medical classic for use at the clinic. We will conduct an observational study using this prescription.

1. Effects of modified SMS in an animal study

There was an animal study showing that SMS was effective in BP regulation. In mice with normal BP, BP was lowered in the high-dose group, and local blood flow also increased dose-dependently in mice with normal BP given SMS. In a preclinical trial, SMS led to reduced NO production in rat aortic VSMC treated with TNF-α + IFN-γ, increased cell viability, and reduced iNOS protein and mRNA production.

A preclinical trial on the use of modified SMS (the investigational product of our trial) confirmed suppression of increased BP. A study on the effects of a three-week modified SMS regimen in mice with HTN induced with L-NAME showed that the BP was lowered to near-normal levels in the SMS group compared to the non-SMS group. In particular, ethanolic extract of modified SMS was more effective than water extract of modified SMS (Figures 2, 3).

In light of the result of the previously mentioned preclinical trial, where SMS reduced the production of vasoconstrictors in VSMC in mice, modified SMS is believed to be a promising therapeutic option for HTN.

[figure not shown]

Figure 2

Graphs summarize systolic BP(A), and diastolic BP(B) (a,***p<0.001 Before L-NAME vs. After L-NAME ; b, *** p<0.001 After Normal vs. After L-NAME). BP was measured using the tail-cuff method. Results are expressed as the mean ±S.E. (n=6 mice per group). Before, L-NAME non-treatment; After, L-NAME treated.

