A study questionnaire will be used to obtain data, and a total of five test parameters will be monitored. The questionnaire and tests will be performed at every visit, and it will take about 30 minutes. The questionnaire and tests will be performed at Kyung Hee Bi, Che, Dam Korean Medicine Clinic, and the PI will be in charge of distributing and collecting the questionnaire and performing tests.

| Item | Screening and enrollment | Treatment phase | | F/U |
| --- | --- | --- | --- | --- |
|  |  | 4wks | 8wks | 12wks |
| Visit | Visit 1 | Visit 2 | Visit 3 | Visit 4 |
| Visit window | 0주 | Week 4 (±7 days) | Week 8  (±7 days) | Week 12  (±7 days) |
| Informed consent | ○ |  |  |  |
| Sociodemographic information | ○ |  |  |  |
| VS and physical examination | ○ | ● | ● |  |
| Compliance with pre-visit instructions | ○ | ● | ● |  |
| Medical history·treatment history·medication history | ○ |  |  |  |
| Inclusion and exclusion criteria | ○ |  |  |  |
| Blood test | ● | ● | ● |  |
| BP and pulse measurement | ○ | ● | ● |  |
| 3D BP waveform test | ● | ● | ● |  |
| European Quality of Life Five Dimension Five Level Scale (EQ-5D-5L) | ● | ● | ● |  |
| Modified SMS prescription and dispensing | ● | ● |  |  |
| Monitoring of herbal medicine adherence and dosage |  | ● | ● |  |
| Monitoring of AEs |  | ● | ● | ● |
| Changes in Medical history·treatment history·medication history ** |  | ● | ● | ● |
| Conclusion of case* |  |  |  | ● |

Table 2. Summary of study data collected by timeline

* Conclusion of case: collected after visits are completed or participant is discontinued

** Changes in Medical history·treatment history·medication history: Collect information upon changes in Medical history·treatment history·medication history since the visit

● Tests performed only on those who qualify per the inclusion/exclusion criteria

eCRF will be identical to the paper-based CRF, and the Mytrial program at NIKOM will be used to establish the eCRF.

Modified intervention records: if the treatment interventions are changed mid-way, the changes will be recorded in the modified intervention record section of the CRF.

Concomitant drugs and treatment: Concomitant drugs and treatment will be recorded in the respective section in the CRF.

1. Management of human-derived materials

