       2. Measurement items: Aspatate transaminase(AST), Alanine transaminase(ALT), Gamma glutamyl peptidase(GGT), Total Bilirubin, BUN, Creatinine, Total cholesterol, Glucose
       3. Measurement method

- Refrain from caffeine, alcohol, and tobacco consumption the day before the test
- 8-hour fasting is required before the test; water allowed
- Test takes 10 minutes

1. [**3D Blood pressure and pulse wave test]**: **3d pulse wave imaging device (3D MAC, ㈜ Daeyomedi Co., Ltd., South Korea)**: 10 minutes ( See [Attachment 1])
   - - 1. Pulse strength value and stage (Unit:gf)
       2. Pulse depth value and stage (Unit:gf/cm^2)
       3. Pulse velocity value and stage (Unit:beats)
       4. Pulse shape value and stage (Unit:step)
       5. Radial artery augmentation index(R-AI) (Unit:%)
       6. SBP (Unit:mmHg)
       7. DBP (Unit:mmHg)
       8. Pulse pressure (PP) (Unit:mmHg)
       9. Pulse rate (PR) (Unit:beats/min)
       10. Cardiac output (1 beat) SV (Unit:mL/beat)
       11. Cardiac output (1 minute) CO (Unit:L/min)
       12. Systemic vascular resistance index(SVRI) (Unit:dyn*s/cm^5/m^2)
2. European Quality of Life Five Dimension Five Level Scale (EQ-5D-5L) questionnaire: 5 minutes ( see [Attachment2] )
3. Other

Adverse events and concomitant treatments are monitored per patient’s report and questions at every visit

1. Outcome measurement criteria and method
2. Primary outcome

This study is an exploratory observational study aiming to explore the safety and BP-lowering effetcs of modified SMS prepared and prescribed by Kyung Hee Bi, Che, Dam Korean Medicine Clinic for patients with HTN by comparing SBP before and after treatment.

1. [Changes in MSSBP] use Omron Healthcare HEM-9000AI
   Amount of change in MSSBP at end of treatment (visit 3) compared to the baseline (visit 1)
   - - 1. Null hypothesis (H0): There is no difference in MSSBP between the baseline (Visit 1) and end of treatment (visit 3).
       2. Alternative hypothesis (HA): There is a difference in MSSBP between the baseline (Visit 1) and end of treatment (visit 3).
2. Secondary outcome
3. Amount of change of MSSBP at visit 2 compared to the baseline (visit 1)
4. Amount of change of MSSBP at visits 2 and 3 compared to the baseline (visit 1)
5. Percentage of participants with normalized BP: percentage of patients who achieved normal BP compared to MSSBP/MSDBP measured at each time point (percentage of patients who had a BP of less than 140/90 mmHg at end of treatment)

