1. Adverse events anticipated from use of modified SMS during routine treatment process

There is a low risk for AEs anticipated due to the use of modified SMS (risk for adverse effects and tolerance to modified SMS), but there is a risk for the following AEs that may occur with the routine treatment protocol:

- Gastrointestinal symptoms (Indigestion, heartburn)
- Autonomic nervous system symptoms (palpitation)

Thus, other than the AEs associated with the use of modified SMS for therapeutic purposes, there is little to no anticipated risks or adverse effects from study participation.

1. Usage precautions

- The participants are educated about the following precautions when taking the herbal medicine:
- Keep the herbal medicine in a cool place or in the refrigerator.
- Once opened, take the herbal medicine as soon as possible, and any opened herbal medicine must be kept in the refrigerator within two days.

1. Education on AEs

The PI and co-investigators of the observational study will inform the participants or their caregivers about the potential AEs following the use of modified SMS during the study period and explain that there is little risk for additional AEs from study participation because the study does not involve additional intervention or tests other than those included in the routine treatment protocol. The participants should also be informed to contact the research team immediately upon developing an AE.

1. Collection and reporting of AEs

At every visit to the Kyung Hee Bi, Che, Dam Korean Medicine Clinic, VS measurements, examination, and questionnaire for the observation parameters, or monitoring of AEs will be performed. If the investigator finds that the participant has clinically significant symptoms or changes and if the study participant voluntarily reports such an event, the investigator will document the incidence, evaluation, and measures for AEs in the CRF using standardized medical terminology.

In case of a serious adverse event (SAE) during study participation, the SAE will be promptly reported via the e-IRB system in accordance with Article 4–25 of the Standard Operating Procedures of the joint IRB. SAE is defined per the Standard Operating Procedures of the joint IRB.

1. Treatment of AEs

If a participant incurs a direct injury from the use of modified SMS as part of the routine treatment process, appropriate medical treatment will be given based on the routine treatment process.

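### Table 2 schedules no adverse-event or symptom question before the first dose, against the text's every-visit rule, so separating old complaints from new ones rests on unstructured history

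*Protocol*

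**What the plan says.** - **Schedule.** In the Method section, Summary of study timeline, Table 2, the row "Monitoring of AEs" is blank at visit 1 and marked at visits 2, 3 and 4. Dispensing is marked at visits 1 and 2.
- **Text.** Section 12.D (Other) states: "Adverse events and concomitant treatments are monitored per patient’s report and questions at every visit". Section 14, under collection and reporting of AEs, says that at each visit to the clinic "VS measurements, examination, and questionnaire for the observation parameters, or monitoring of AEs will be performed".
- **Anticipated events.** Section 14.B lists two groups only: gastrointestinal (indigestion, heartburn) and autonomic (palpitation). The background section says the clinic uses the product in general "to treat CVD or autonomic nervous system symptoms".
- **What visit 1 does collect.** Table 2 marks medical, treatment and medication history, vital signs and physical examination, blood test, blood pressure and pulse, pulse-wave test and EQ-5D-5L. Changes in history are marked at visits 2 to 4. Section 12.B names the history items only as history, surgical history and medication history.
- **Counting and analysis.** Section 14 has the investigator document clinically significant symptoms or changes. Section 14.G evaluates all AEs in the study period and also presents those associated with the intervention. Section 16 presents drug reactions and serious events as n (%) and compares time points by McNemar or exact McNemar test.
- **Design.** There is one group and no control. Exploring safety is part of the stated purpose.

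**The concern.** The three anticipated events are all symptoms, known only by asking the patient, and all are common complaints that can precede treatment. Palpitation also belongs to the symptom class for which the clinic uses the product. With no control group, the patient's own state before the first dose is the only comparator. If nobody asks about these symptoms before dispensing, a long-standing complaint first elicited at visit 2 may be counted as an AE in one patient and set aside as pre-existing in another. The reported rate would then not be the rate of new or worsened symptoms. AE counts are also part of the criterion for early termination in section 17, although that criterion is limited to moderate or severe events judged related.

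The schedule and the text also disagree on whether there is a question at visit 1, and the site cannot follow both.

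**Working it through.** **1. Pre-dose value by type of safety information (Table 2 and sections 12 and 14)**

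| Information | Visit 1 | Visit 2 | Visit 3 | Visit 4 |
| --- | --- | --- | --- | --- |
| Blood test | yes | yes | yes | no |
| Vital signs, examination | yes | yes | yes | no |
| Medical, treatment, medication history | full | changes | changes | changes |
| AE monitoring per Table 2 | no | yes | yes | yes |
| AE monitoring per section 12.D | yes | yes | yes | yes |
| Named question on palpitation, indigestion, heartburn | none | none | none | none |

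Laboratory values and vital signs have a scheduled pre-dose measurement. The anticipated symptoms have only whatever the general history happens to capture. Taking section 12.D at its word, a visit 1 question is intended but its content is not given. Taking Table 2 at its word, there is none. On either reading no pre-dose record of the three symptoms is specified.

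**2. Counting rule.** In the text shown, section 14 triggers documentation on symptoms or changes, and section 14.G counts all AEs. Neither requires that a symptom be new or worse than before dosing.

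**3. McNemar comparison.** The test needs the same yes/no item in the same patient at two time points. With AE monitoring at visits 2, 3 and 4, the available pairs are 2 with 3, 2 with 4, and 3 with 4. None contains a pre-dose value. A drug reaction cannot exist before the drug, so a before-and-after comparison is meaningful only for the presence of the symptom, and that is the item not scheduled at visit 1.

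**4. Headcount.** The plan's own figure reproduces: 20 evaluable with 33% dropout gives 20 / (1 − 0.33) = 29.85, rounded up to 30. It is used here only as the number of patients.

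**5. Upper bound on misclassified patients.** The documents give no prevalence of these symptoms before dosing, so p = 10% to 40% is an assumption. The bound is N × p:

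- N = 30: 30 × 0.10 = 3, 30 × 0.40 = 12.
- N = 20 returning: 20 × 0.10 = 2, 20 × 0.40 = 8.

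This supposes that every prior complaint persists, is reported later, is counted as an AE, and is missed by the visit 1 history. Each condition that fails lowers the number.

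**6. Will the situation arise at all?** The chance that at least one of 30 patients has such a complaint beforehand is 1 − (1 − p)^30. At p = 5% this is 79%, and at p = 10% it is 96%. The site should expect to have to make this classification.

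**The case against.** The case on the other side is substantial.

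- Starting AE recording after the first dose is ordinary practice. A complaint present before dosing is history, not an AE, so a blank visit 1 cell is not an error in itself. This stands. The fault is the conflict with the text and the lack of a specified baseline for the symptoms the protocol itself expects.
- Visit 1 history and examination, with changes in history at visits 2 to 4, are the usual route for recognising pre-existing complaints. The section on protecting personal information adds that further items usual in Korean medicine practice are collected. This also stands. A reader might infer that old and new complaints cannot be separated at all, or that the prescriber would sort them from memory. The documents do not support either reading: history and AEs are recorded, and monitors check CRF data against source documents. Separation is partial and unstructured, not absent.
- The autonomic indication is the clinic's general use. Participants enter on blood pressure, and angina and severe arrhythmia are excluded, which may make prior palpitation less frequent. So the indication does not show that many participants have such symptoms.
- The contents page lists a definition of AEs in section 15.A that is not in the text at hand and may contain a new-or-worse rule. If it does, the rule still needs a visit 1 answer to be applied.
- No fixed questions are described for visits 2 to 4 either, so there is no instrument to copy back to visit 1. True, and for that reason the fix covers all visits.
- Section 12.D may mean every visit after dosing, and the wording in section 14 is loose enough to allow Table 2. If so, the conflict is one of wording, but the missing baseline remains.

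**Conclusion.** The point holds in limited form and is worth acting on. Table 2 and sections 12.D and 14 disagree about visit 1, and no pre-dose record of palpitation, indigestion or heartburn is specified. Classification of these symptoms therefore depends on general history, so AE rates may be inflated or inconsistent between patients, and the across-time McNemar comparison has no scheduled pre-dose value.

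The size is not known. On an assumed prior prevalence of 10% to 40%, the ceiling is 3 to 12 of 30 patients, or 2 to 8 of 20. It would be tempting to read this as an apparent AE rate of 10% to 40% against a true rate of zero. That is the worst case with visit 1 history ignored, and nothing in the documents supports it as an expectation. The conclusion rests on the text shown: the AE definition in section 15.A and the CRF are not at hand.

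**What to change.** 1. Reconcile Table 2 with sections 12.D and 14 by adding a visit 1 entry, before dispensing, that records palpitation, indigestion and heartburn by presence and severity.
2. Ask the same questions at visits 2, 3 and 4. Visit 4 is by telephone, and the questions can be asked that way.
3. In section 14.G, report as treatment-emergent only symptoms that are new or worse than at visit 1, and show the visit 1 frequency beside the on-treatment frequency.
4. In section 16, state which time points the McNemar test compares. For these symptoms, use presence at visit 1 as the pre-dose value.

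The cost is a minute or two at visit 1, a few CRF fields and short additions to sections 14.G and 16. No visit, test or staff is added. The visit 1 answer cannot be recovered once dosing has begun, so the change has to be made before enrolment.

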4. Liver disease or kidney disease requiring treatment
5. Secondary hypertension
6. History of severe CVD: e.g., myocardial infarction, angina, severe arrhythmia
7. Diagnosis of psychiatric disorder or treatment for psychiatric disorder, including depression, within 2 months of visit
8. Other reasons that contraindicate use of modified SMS as determined by the clinician

- (*Reference arm is selected based on the process outlined in “12. Observation parameters-B.Measurement items”)
- (*Mean seated BP is defined in “12. Observation parameters-B.Measurement items”)

1. Control group

A prospective single-group preliminary observational design; there is no control group, and blinding and randomization are not applicable.

1. Anticipated sample size and grounds for sample size determination

This is an exploratory preliminary prospective observational study. In general, preliminary studies require a minimum of 12 participants [9]. In the present study, we aim to obtain data from 30 participants.

F/u is performed every 4 weeks. In general, 67% of participants re-visit the facility on week 4.

To obtain data from 20 participants with a potential 33% dropout rate, **30 participants** are required.

Every month, about 10 patients take modified SMS, so recruiting the target sample size within the study period is feasible.

In preliminary studies, a minimum of 12 participants are generally required. **Given that this study is a preliminary study collecting exploratory data for subsequent studies, as opposed to a study investigating the therapeutic efficacy, recruitment of 30 participants in consideration of potential dropouts is deemed adequate.**

1. Participant recruitment

Participants will be recruited among patients who visit the Kyung Hee Bi, Che, Dam Korean Medicine Clinic and based on the clinician’s assessment and patient consent.

To ensure consistency of recruitment and fairness for potential participants, a recruitment announcement containing the overall information about the study, including its purpose, inclusion and exclusion criteria, and study schedule, will be posted on the bulletin board within the clinic for a specified period. Visitors to the healthcare facility interested in participating in the study can contact via the contact details listed in the announcement or by directly contacting the research team (PI and co-investigators).

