- The study is conducted under a national research and development project commissioned by the National Institute for Korean Medicine Development (NIKOM) (evidence-generating research as part of Korean medicine innovative technology development project). The research data collected according to the study announcement will be recorded and stored through E-CRF (Mytrial) established by NIKOM and provided to them. Provision of the study data to a third party and use of the data for secondary studies will be permitted only after obtaining a separate consent from from the participants for the purpose.

1. Method
2. Outline of method
3. Study period

Anticipated study period (1 year from approval date. Scheduled to be completed by August 31, 2024)

1. Study site

Kyung Hee Bi, Che, Dam Korean Medicine Clinic; a prospective observational study on patients

1. Study design

Single-group, prospective, exploratory, preliminary observational study

This study is an observational study for preliminary exploration of the therapeutic effects of modified SMS on HTN and for exploration of feasibility for future randomized controlled trial.

1. Study schedule (standard management protocol): 4 clinical assessments

Baseline (wk 0, screening and enrollment, visit 1)

Mid-treatment (4 weeks after beginning dosing of modified SMS) (visit2)

End of treatment (8 weeks after beginning dosing of modified SMS) (visit3)

4-week f/u after treatment (12 weeks after beginning dosing of modified SMS) (visit4)

1. Standard protocol for modified SMS

The participants will undergo the following process per the standard protocol:

When using modified SMS, those receiving any other KM treatments, including acupuncture, pharmacopuncture, and moxibustion, will be excluded

1. Standard herbal medicine prescription protocol

- Compliance with pre-visit instructions:
  After making an appointment for the visit, patients are instructed to fast for 8 hours before the visit, refrain from smoking, drinking, and consuming caffeine the day before the visit, and to visit the clinic between 8–12 AM.
- History taking
- 3D BP waveform test (3-d pulse imaging study), blood test
- Same tests performed at F/u on weeks 4, 8, and 12 after herbal medicine prescription

1. Standard protocol visits

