- (Visit) Patients who take herbal medicine prescribed by Kyung Hee Bi, Che, Dam Korean Medicine Clinic are instructed to make f/u visits every 4 weeks for monitoring of AEs and clinical progress. In case of AEs, additional visits may be necessary.

1. Standard protocol tests

- The Standard management protocol at Kyung Hee Bi, Che, Dam Korean Medicine Clinic involves performing 3D BP waveform test and blood tests on patients taking herbal medicines every four weeks. In the present study, only patients taking modified SMS were enrolled. However, additional tests may be performed in cases of AEs.

1. Study intervention: administration of modified SMS per standard protocol

In the present study, we modified the traditional SMS formula used for CVD (ginseng, Ophiopogon japonicus, and Schisandra chinensis) based on clinical experience, classic texts, and experiment findings. We removed ginseng and added Platycodon grandiflorus and Pueraria lobata as well as Dioscorea opposita and Coix lacrymajobi to stimulate digestive functions. The formula consisting of **Pueraria lobata (5.33g), Platycodon grandiflorus (5.33g), Ophiopogon japonicus (5.33g), Dioscorea opposita (2.67g), Coix lacrymajobi (2.67g), and Schisandra chinensis (2.67g) (total 24g; unit g/day)** is referred to as saengmaeksangagambang (modified SMS). This is one of the unique empirical prescriptions used at Kyung Hee Bi, Che, Dam Korean Medicine Clinic. Although in actual practice at Kyung Hee Bi, Che, Dam Korean Medicine Clinic, **certain ingredients may be removed, doses may be adjusted, or other interventions such as acupuncture, may be added depending on the symptoms and disease being treated, such cases were excluded from the analysis in this study.**

- Patients take a 60-mL 70% alcohol-soaked decoction of the modified SMS formula prepared by Kyung Hee Bi, Che, Dam Korean Medicine Clinic twice daily before meals or between meals
- Dispensing of medicine on Visit 1, Visit 2: [number of days until next scheduled visit date (standard 28 days, maximum 35 days) + 3 days]* 2 packs. A standard of 62 packs, up to 76 packs, are packaged in a box or pack, labeled with the patient’s information.
- Participants will return unused medicine at the subsequent visit.
- Returned unused medications will be stored separately for each patient in a box/pack.
- At completion of trial, returned medicines will be disposed of following the facility’s medication disposal procedures.

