- Dose per pack: modified SMS: each pack contains 60 mL containing Pueraria lobata (5.33g), Platycodon grandiflorus (5.33g), Ophiopogon japonicus (5.33g), Dioscorea opposita (2.67g), Coix lacrymajobi (2.67g), and Schisandra chinensis (2.67g) (total 24g; unit g/day).
- Dosage: oral; 2 packs a day
- Treatment period: 8 weeks (56 days) (f/u every 4 weeks)
- Permitted concomitant treatments: Given the observational nature of this study, we will not limit any concomitant treatments and medications while undergoing the SMS regimen, and concomitant treatments will be documented.
  * Use/non-use of antihypertensive drugs will be documented.
  * If antihypertensive drugs are being used, patients are informed to notify the investigator upon changes in the dose and dosage of the drug.
  * Patients are informed to maintain their normal lifestyle, including exercise and diet.
- The dose and dosage of modified SMS used in this trial are identical to those used in actual practice at Kyung Hee Bi, Che, Dam Korean Medicine Clinic.

|  | | |
| --- | --- | --- |
| [figure not shown] | [figure not shown] | [figure not shown] |
| Cold extraction | Vacuum concentration | Concentrate |

Figure 5. Preparation facilities at Kyung Hee Bi, Che, Dam Korean Medicine Clinic and appearance of concentrates

1. Additional interventions, visits, and tests required for study participation per the purpose

The Standard management protocol at Kyung Hee Bi, Che, Dam Korean Medicine Clinic involves performing 3D BP waveform test and blood tests on patients taking herbal medicines every four weeks. In the present study, only patients taking modified SMS were enrolled. **Thus, there are no additional interventions required for participation in this study**

**In case of an adverse event, f/u is needed until the adverse event is resolved. In such cases, additional visits may be necessary.**

In case of an adverse event, additional tests, such as kidney function test, liver function test, and complete blood count, may be performed.

1. Control group, randomization, blinding

This is a single-group study without a control group, so randomization and blinding are not applicable.

1. Summary of study timeline (anticipated duration, place, staff in charge, study procedure)

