Full Analysis Set(FAS): Per the Intention-to-Treat (ITT) principle, FAS includes participants who have received the herbal medicine preparation at least once and have had at least one measurement of the primary outcome measure

Safety Set (SS): Includes participants who have received the herbal medicine preparation at least once and have had at least one safety-related f/u

For demographic and baseline data, categorical data will be presented as n (%), and continuous data will be presented as mean±SD.

For efficacy parameters, continuous variables will be analyzed with paired t-test or Wilcoxon signed rank test, and categorical variables will be analyzed using the McNemar test or McNemar Exact test depending on their normality.

For safety parameters, adverse drug reactions (ADRs), SAEs, and serious ADRs will be presented as n (%), and differences across time points will be analyzed using the McNemar test or McNemar Exact test.

ANCOVA model will be used for analysis with sociodemographic factors that may affect HTN, such as sex, age, and use of antihypertensive drugs, included as covariates.

1. Withdrawal of consent and discontinuation
2. Discontinuation criteria

Participants may be discontinued from the trial in the following instances:

- Participants or their legal representatives requests discontinuation or participant withdraws consent due to unsatisfactory treatment effects during the study period
- Violation of inclusion criteria or meeting exclusion criteria
- Failure to take the modified SMS even once during the observational study period, despite giving consent and meeting eligibility criteria
- Occurrence of SAE related to the herbal medicine or AE making continuation in the study difficult
- Change of prescription during study
- Participant’s violation of study plan
- Lost to f/u during study period
- Other reasons due to which continuation of study is deemed inappropriate by the investigator

1. Study termination criteria

Upon occurrence of SAE suspected to be caused by the investigational drug, the PI notifies the joint IRB within 24 hours and terminate the study.

The clinical trial may be terminated prematurely in the following cases:

- Harmfulness of investigational product is discovered
- Moderate or severe AE deemed to have a relationship with the clinical trial occurred in more than 25% of the entire study population
- Study poses threat to the safety and well-being of study participants

1. Withdrawal of consent

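### Visit 4, the only scheduled AE contact after treatment, is timed from start of dosing and is not fixed for early stoppers or visit-missers; dosed participants never reached leave the Safety Set

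*Protocol*

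**What the plan says.** **Timing.** The study schedule in the Method section describes visit 3 as "End of treatment (8 weeks after beginning dosing of modified SMS) (visit3)" and visit 4 as "4-week f/u after treatment (12 weeks after beginning dosing of modified SMS) (visit4)". Table 2 gives visits 3 and 4 each a window of ±7 days. The standard herbal protocol states "Treatment period: 8 weeks (56 days) (f/u every 4 weeks)". The dispensing rule at visits 1 and 2 is "number of days until next scheduled visit date (standard 28 days, maximum 35 days) + 3 days]* 2 packs", and unused medicine comes back at the next visit.

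**Who is contacted.** Table 2 schedules AE monitoring at visits 2, 3 and 4. The compensation section says that visit 4 is by telephone. The Table 2 footnote reads "Conclusion of case: collected after visits are completed or participant is discontinued". An AE that has occurred is followed until it resolves (sections on additional interventions and on treatment of AEs), and participants are told to contact the team at once if they develop one (education on AEs).

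**Who is counted.** The Safety Set is defined thus: "Includes participants who have received the herbal medicine preparation at least once and have had at least one safety-related f/u". The sample-size section states "In general, 67% of participants re-visit the facility on week 4" and allows for 33% dropout. Loss to follow-up is among the reasons for which a participant may be discontinued.

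**What is kept.** The section on withdrawal of consent excludes and discards the data of anyone who withdraws or meets a discontinuation criterion. The section on evaluation of safety parameters promises the rate of AEs that led to discontinuation.

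**The concern.** Safety is one of the two things the study sets out to explore, and the protocol promises rates for all AEs in the study period. Such a rate needs a defined period of asking and a defined group who are asked. Neither is secure here.

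Visit 4 has two anchors, which agree only when the last dose falls on day 56 and the call on day 84. For someone who stops early, or who takes the product and misses visits, the protocol fixes no contact counted from the last dose and does not say that the week-12 call is still made. New or unreported AEs in these people then depend on spontaneous report. If they are never reached, the Safety Set definition removes them.

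Loss in a single-arm study of this kind may well be related to tolerability. The people about whom least is asked could be those with most to report, and no later analysis can recover events that were never collected.

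**Working it through.** **1. The plan's own figure.** From the sample-size section, 20 participants with data and 33% dropout give 20 / (1 − 0.33) = 29.85, rounded up to 30. The stated 30 is reproduced.

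**2. Visit windows in days from start of dosing (Table 2).**
- Visit 3: 56 ± 7, days 49 to 63.
- Visit 4: 84 ± 7, days 77 to 91.

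**3. How far dosing can run.** The rule supplies (28 + 3) × 2 = 62 packs as standard and (35 + 3) × 2 = 76 packs at most. At 2 packs a day that is 31 and 38 days. With visit 2 on day 28 and the maximum 35 days to visit 3, supply covers dosing to day 63. The stated treatment period is 56 days. The document does not say whether a participant with a late visit 3 stops on day 56 or at the visit.

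**4. Interval from last dose to visit 4 under each reading.**

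| Last dose | Shortest (days) | Longest (days) |
| --- | --- | --- |
| At visit 3 | 77 − 63 = 14 | 91 − 49 = 42 |
| Fixed at day 56 | 77 − 56 = 21 | 91 − 56 = 35 |
| Earlier of visit 3 and day 56 | 77 − 56 = 21 | 91 − 49 = 42 |

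The stated interval is 4 weeks, 28 days. Anchoring the call to the actual last dose with the existing window gives 28 ± 7 = 21 to 35 days under every reading, and for early stoppers as well.

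**5. Early stoppers.** Side by side, the footnote lets the case be concluded at discontinuation, the AE sections follow events already known, and no section fixes a solicited contact after stopping. The guaranteed period of solicited follow-up for new AEs is therefore nil. That describes what is fixed, not what must happen in practice.

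**6. Size of the possible loss from the Safety Set.** Non-return at week 4 is 30 × 0.33 = 9.9, about 10. Anyone who attends visit 2 has had a safety follow-up, so on this figure 10 is the ceiling. It is reached only if none of the 10 has any later safety contact. The Safety Set would then be about 20.

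**7. What that does to precision alone.** With no events seen, the one-sided 95% upper bound for an event rate is 1 − 0.05^(1/n):
- n = 30: 9.5%.
- n = 20: 13.9%.

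This ignores any link between loss and AEs, which could bias the rate further by an amount the document gives no means to estimate.

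**8. What a change of denominator does alone.** If x of 20 contacted participants have an AE and the other 10 stay unreached, the rate over all dosed is x/30, which is 20/30 = 0.67 of the rate among those contacted. An all-dosed denominator without the calls treats the unreached as free of AEs.

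**The case against.** A reader might infer that AE surveillance ends at discontinuation and that early stoppers are never called. The documents do not say so. The footnote governs when a case-conclusion item is collected; it does not cancel visit 4. Because visit 4 is counted from start of dosing, an early stopper could still be called at week 12. This stands: the defect is that the contact is not fixed, not that it is ruled out.

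A reader might also infer that people who stop because of an AE fall out of the Safety Set. Someone who reports the AE is observed until it resolves and so has a safety-related follow-up. This stands too, and the gap is confined to new or unreported events in people not reached again.

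On the numbers, the 14-day end needs dosing past the stated 56 days, and the 42-day end is longer follow-up rather than a safety gap. On a strict 56-day reading, a re-anchored call gives completers the same 21 to 35 days. The 67% is a general clinic figure, whereas study participants are paid for visits 1 to 3 and have their schedules arranged individually. Ten of 30 is thus an upper bound and not a forecast.

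Finally, requiring a post-dose safety assessment is a defensible convention, and enlarging the denominator alone can understate the AE rate. That is a reason to report both denominators. It does not remove the need for the contact.

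**Conclusion.** The point holds as a gap in what the protocol fixes, and it should be closed. Visit 4 carries two anchors: 14 to 42 days after last dose if dosing ends at visit 3, and 21 to 35 days if it ends on day 56. The sections on treatment length, dispensing and visit windows must be reconciled; this review takes no view on which treatment length is meant.

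For participants who stop early or miss visits, no solicited AE contact is guaranteed, although known events are followed. On the protocol's own non-return figure, at most about 10 of 30 dosed participants could leave the Safety Set. That bound assumes the general clinic figure applies to the study and that none of the 10 has any later safety contact. The resulting AE rate may describe mainly those who stayed; the documents give no AE rates from which to size that bias.

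One contradiction bears directly on the remedy: discarding the data of everyone who meets a discontinuation criterion cannot stand beside a promised rate of AEs leading to discontinuation. Left as it is, that rule could remove whatever extra calls collect.

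**What to change.** - State that the existing visit 4 telephone AE call is made to everyone who took at least one dose, including early stoppers and those who miss visit 2 or 3, unless they refuse contact. Time it 4 weeks (±7 days) after the actual last dose, which is the protocol's own interval and window.
- Complete the case-conclusion item after that call or after documented failed attempts.
- Report AE rates over all dosed participants and over those with at least one safety contact, with the number never reached.
- Reconcile the data-discard rule under withdrawal of consent with the promised rate of AEs leading to discontinuation, so that safety data from discontinued participants are kept as far as consent allows.
- Reconcile the stated treatment length, dispensing rule and visit windows, so that the date of last dose is well defined.

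The cost is a few extra telephone calls by staff who already make the visit 4 call, plus edits to Table 2, the study schedule, the Safety Set definition and the withdrawal section. The drawback is that completers' calls no longer fall on a common week from start of dosing. Anyone still unreached counts as AE-free in the all-dosed rate, which is why the second rate and the number never reached go beside it.
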